#### *Tuina* Experimental Group

Participants will receive 20-minute pediatric *tuina* treatments. The treatments will be administered 3 times a week for a total of 8 weeks. A professor specializing in pediatric *tuina* will determine the specific techniques. The techniques will require a light and gentle touch, steady and substantial. Children will be placed in a quiet and warm treatment room with a temperature maintained between 25 °C and 28 °C, ensuring they are in a state of calm. The specific steps are as follows: (1) Step 1: holistic regulation; (2) Step 2: selective stimulation of back-sensitized acupoints; (3) Step 3: symptomatic treatment; and (4) Step 4: harmonization of Yin and Yang.

First, based on the holistic concept and the principle of adhering to the disease mechanism, we will apply *tuina* to the Governor Vessel (GV) and the Bladder Meridian of Foot-Taiyang (BL):

The child will be placed in a prone position, with the practitioner standing on the right side of the child. They will use the thumb to knead the entire spine in the direction of the GV from top to bottom, 3 times for 1 minute.The practitioner will knead the first and second lateral lines of the bladder meridian from top to bottom using the index and middle fingers, 3 times for 1 minute.The practitioner will use the thumb and index finger to pinch and lift the skin of the spinal column surface, performing this action from bottom to top 3 times in 1 minute.The practitioner will rub the acupoints of BL 23, GV 4, and BL 31‐34, using the palm or the thenar eminence to firmly press against the skin and perform rapid linear reciprocating rubbing movements for 1 minute (Figure 2).

**Figure 2. F2:**
[figure not shown]
Holistic regulation. Step 1 of selected spinal manipulative therapy. BL: Bladder Meridian of Foot-Taiyang; GV: Governor Vessel.

Second, the child will remain in a prone position, and the practitioner will stand on the right side. The practitioner will perform palpation of the cervical and dorsal regions to identify positive reaction points (linear or nodular reaction points). We will confirm the sensitized acupoints using infrared thermography. The practitioner will perform targeted stimulation using kneading manipulation for 2 minutes (Multimedia Appendix 1).

Third, for symptoms of dry eyes and blurred vision, the practitioner will apply the kneading technique to BL 1, BL 2, Eight Extraordinary Meridians-Head and Neck (EX-HN) 4, Triple Energizer Meridian of Hand-Shaoyang (TE) 23, Stomach Meridian of Foot-Yangming (ST) 1, and ST 2, with each acupoint treated for 1 minute, totaling 6 minutes. They will gently rub both palms together to generate heat and then apply the warmth to the eyes for 1 minute (Figure 3).

**Figure 3. F3:**
[figure not shown]
Symptomatic treatment. Step 3 of selected spinal manipulative therapy. BL: Bladder Meridian of Foot-Taiyang; EX-HN: Eight Extraordinary Meridians-Head and Neck; ST: Stomach Meridian of Foot-Yangming; TE: Triple Energizer Meridian of Hand-Shaoyang.

Fourth, the child will assume a supine position, and the practitioner will stand on the side of the child’s head. The practitioner will alternately push the “Tianmen” and the “Kangong” with both thumbs 50 times for each and knead EX-HN5 for 1 minute with the middle fingers, totaling 2 minutes. The practitioner then will use the thumbs to knead Large Intestine Meridian of Hand-Yangming (LI) 20 and the palm to rub GV 22 and GV 20 circularly for 1 minute each, totaling 3 minutes. We will then place the patient in a sitting position, and the practitioner will lightly pat the back with a hollow palm, performing this 3 times from top to bottom, for 1 minute. The thumb and index finger, along with the middle finger, will pinch the BL 17 3 times for 1 minute (Figure 4).

**Figure 4. F4:**
[figure not shown]
Harmonization of Yin and Yang. Step 4 of selected spinal manipulative therapy. EX-HN: Eight Extraordinary Meridians-Head and Neck; GV: Governor Vessel; LI: Large Intestine Meridian of Hand-Yangming.

For the location and manipulation details of each acupoint, see Multimedia Appendix 1.

#### Drug-Positive Control Group

The positive-drug control group will receive treatment with compound tropicamide eye drops (Shenyang Xingqi Co., Ltd.; product specification: 1 ml per vial) at a frequency of once every 2 days before bedtime, with 2 drops per administration. The group will continue the treatment for a duration of 8 weeks.

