**Methods:**

This study is a multicenter randomized controlled clinical trial. A total of 62 children with myopia will be recruited from 4 hospitals and randomly assigned in a 1:1 ratio to a *tuina* experimental group and a drug-positive control group (tropicamide eye drops). Treatments in each group will be administered 3 times per week for a total of 8 weeks. The *tuina* experimental group will receive 20 minutes of *tuina* therapy per session, while the drug-positive control group will receive tropicamide eye drops administered every other day, with 2 drops per session. The primary outcome measures include uncorrected visual acuity and axial length, while secondary outcome measures include refractive power and accommodative amplitude. Data will be collected at baseline (week 0), on the day of completion of weeks 4 and 8 of treatment, and at the end of the 10-week follow-up period. Adverse events will be monitored and recorded throughout the study. Statisticians will be blinded. Data will be analyzed using SPSS version 28.0.

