## Methods

### Study Design

This study is designed as a multicenter randomized controlled noninferiority trial to be conducted from June 2025 to October 2026. We plan to recruit 62 participants from 4 hospitals in Yunnan Province. Eligible participants will be randomly assigned in a 1:1 ratio to the *tuina* experimental group and the positive drug control group (tropicamide eye drops). Each participant will undergo an 8-week treatment period followed by a 2-week follow-up. Baseline information and outcomes will be assessed at baseline, at the completion of weeks 4 and 8 of treatment, and at the end of the 10-week follow-up (Figure 1). This trial adheres to the guidelines of the SPIRIT (Standard Protocol Items: Recommendations for Interventional Trials).

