### Adverse Events Reporting and Compliance Enhancement

From week 0 to week 10, detailed records of adverse events (AEs) will be documented, including type, occurrence time, severity, and duration. In the event of visual impairment, skin injuries, fainting, infections, or other serious AEs, treatment will be discontinued, and the participant will be transported to the nearest hospital. A detailed AE report will be submitted to the Ethics Committee. At the conclusion of the follow-up period, children are entitled to receive 3 sessions of pediatric *tuina* therapy at no cost; however, those who withdraw prematurely are not eligible for this benefit.

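### Tuina children have 24 practitioner sessions, while no control-arm contact is described between the week 4, 8 and 10 visits, so the adverse event comparison is at risk of ascertainment bias of unknown direction

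*Protocol article*

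**What the plan says.** All references are to the protocol article.

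- **Tuina arm** (Tuina Experimental Group): "The treatments will be administered 3 times a week for a total of 8 weeks". Each session lasts 20 minutes and is given in person. Under Selection of Therapists and Participants, the therapists must be qualified physicians.
- **Control arm** (Drug-Positive Control Group): the drops are given "at a frequency of once every 2 days before bedtime, with 2 drops per administration", for 8 weeks. The section does not say where, or by whom.
- **Visits for both arms** (Study Design): assessments take place at baseline, then "at the completion of weeks 4 and 8 of treatment, and at the end of the 10-week follow-up".
- **AE recording** (Adverse Events Reporting and Compliance Enhancement): the rule reads "From week 0 to week 10, detailed records of adverse events (AEs) will be documented, including type, occurrence time, severity, and duration". The Abstract adds: "Adverse events will be monitored and recorded throughout the study". Data Management and Quality Control has researchers complete the case report form (CRF) promptly and record AEs whether or not they are related to treatment, with blurred vision and photophobia as examples.
- **Blinding** (Randomization and Blinding): blinding of therapists and guardians is described as difficult, and outcome assessors are to be blinded.
- **Safety claim** (Objectives, repeated in substance in the Abstract and in Expected Findings): tuina is hypothesised to be safer than the drug.

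**The concern.** Safety relative to the drug is one of the trial's stated hypotheses, so the AE comparison between arms must be interpretable. A single recording window of weeks 0 to 10 gives both arms the same rule, but not the same chance that an event comes to anyone's notice. On the stated schedule a tuina child meets a physician-therapist every two or three days. A control child takes a drop at night, and the article describes no contact until the next assessment, up to four weeks later. The plan asks for the time and duration of each event. For a brief episode of blur or photophobia in a control child those details would rest on recall, unless there is contact that the article does not describe.

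If capture differs by arm, the difference in recorded AE rates mixes the effect of treatment with the effect of being seen more often. The question is already live: the Results section reports no AEs with 29 children enrolled (16 tuina, 13 control), in a sentence about tuina that leaves the control-arm count unclear.

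**Working it through.** The article gives no contact count, AE rate or capture probability, so there is no stated figure to reproduce. Step 1 uses only the document. Steps 2 and 3 rest on assumptions and show how the risk would operate, not how large it is.

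**1. Contacts described after baseline**

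- Tuina sessions: 3 per week × 8 weeks = 24.
- Assessments in both arms: weeks 4, 8 and 10 = 3.
- Tuina total: 24 + 3 = 27 if all assessments are separate occasions. The Abstract puts the two on-treatment assessments on the day weeks 4 and 8 are completed. If both fall on session days, the total is 24 + 1 = 25.
- Control total described: 3.
- Within the 8 treatment weeks: 24 to 26 against 2.
- Longest gap between described contacts during treatment: 2 to 3 days with tuina (sessions spread over the week) against 28 days with control.

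**2. Effect of unequal capture on recorded rates**

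Recorded rate = true risk × probability of capture. Assumptions: true risk 20% in both arms, 31 children per arm as planned, capture 90% with tuina.

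| Capture, tuina v control | Recorded rate | Ratio | Expected children with a recorded AE, of 31 |
|---|---|---|---|
| 0.9 v 0.9 | 18% v 18% | 1.0 | 5.6 v 5.6 |
| 0.9 v 0.7 | 18% v 14% | 1.29 | 5.6 v 4.3 |
| 0.9 v 0.5 | 18% v 10% | 1.8 | 5.6 v 3.1 |
| 0.9 v 0.3 | 18% v 6% | 3.0 | 5.6 v 1.9 |

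For example, 0.20 × 0.9 = 0.18 and 0.20 × 0.5 = 0.10. The ratio depends only on the two capture probabilities. With equal elicitation it is 1.0.

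**3. Extreme case: an event is noted only if it is present at a contact**

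Assumptions: onset uniform over 56 days; tuina sessions on days 1, 3 and 5 of each week plus assessments on days 28 and 56; control contacts on days 28 and 56 only; no recall and no report between contacts.

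- Event lasting 1 day: tuina 26 × 1 / 56 = 46%; control 2 × 1 / 56 = 4%.
- Event lasting 3 days: tuina 100% (no gap exceeds 3 days); control 2 × 3 / 56 = 11%.
- Event lasting 7 days: tuina 100%; control 2 × 7 / 56 = 25%.

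Families do recall and report events, so real capture would be less unequal than this.

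**4. Direction**

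More contact alone would record more events with tuina, which works against the hypothesis that tuina is safer. Open-label therapists and guardians who expect tuina to be harmless could push the other way. So could the CRF's named examples, which are visual symptoms; the Introduction lists photophobia as a common complication of atropine, the drug with which it compares tropicamide. Nothing in the document allows these forces to be weighed.

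**5. A related inconsistency**

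The Abstract says: "Treatments in each group will be administered 3 times per week for a total of 8 weeks". That is 24 administrations in each arm. Dosing every second day for 8 weeks gives 56 / 2 = 28. The two statements must be reconciled. The Abstract's sentence could also be misread as a control-arm contact schedule equal to the tuina one.

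**The case against.** The strongest reply is that the article states one AE rule for both arms and that the method of asking between visits (diary, telephone call) is operational detail an article may leave to the full protocol, which is not shown. Prompt CRF completion by researchers, with blurred vision and photophobia named, suggests that such events are expected to be captured. Unequal contact is also inherent in comparing a practitioner-delivered therapy with eye drops, and AEs are not among the listed primary or secondary outcomes.

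Much of this stands, and it limits what can be said. A reader might infer any of the following, and the document supports none of them:

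- **The safety comparison is biased.** Only a risk is shown. A diary or calls in both arms, if the full protocol has them, would largely answer the point.
- **Weeks 4, 8 and 10 are the control arm's only contacts.** Study Design lists assessments. It does not rule out other contact, and home dosing is an inference from the bedtime timing.
- **Tuina events depend on the therapist's own report.** CRF completion is assigned to researchers.
- **Neither a safer nor a not-safer result could be interpreted.** If extra contact dominated, fewer recorded tuina events would be a conservative finding.

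The reply does not remove the stated schedule itself. The imbalance in contact is written into the design, a common recording window does not equalise the chance of detection, and neither the AE section, the data management section nor the blinding section describes an offsetting measure.

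**Conclusion.** The point holds as a risk. The document fixes 24 face-to-face sessions in one arm, describes no contact between assessments in the other, describes no equal elicitation of AEs, and makes a comparative safety claim. The only size the document supports is the contact count: 25 to 27 against 3 after baseline. That ratio does not measure bias. The size of any bias cannot be computed and its sign is unknown. The recorded rates of 18% against 6% to 14% rest wholly on an assumed 20% true risk and assumed capture of 90% against 30% to 70%.

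The weakness concerns the safety comparison. It does not touch the visual acuity or axial length outcomes. It is worth correcting because the remedy is cheap and recruitment is still open.

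**What to change.** 1. At the existing week 4, 8 and 10 visits, have guardian and child in both arms complete the same fixed symptom checklist with the same look-back period. Make it a written form that goes straight to the CRF. The therapist should not handle it, and the blinded outcome assessor should not see it, because answers about drops or massage would reveal the arm.
2. Name the checklist data as the basis of the primary between-arm AE comparison.
3. Report all other AEs (noted at tuina sessions or reported spontaneously, including every serious event) in full by arm beside that comparison, stating how each came to light.
4. State where the drops are given and whether control families have any contact between assessments. Reconcile the Abstract's treatment frequency with the Drug-Positive Control Group section.

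Cost: a short form at visits that already take place, with no added visit and no change to treatment. Some limits remain. Recall runs over up to 4 weeks in both arms, and families still report knowing the treatment. Children who have already passed these visits will lack some checklist data: 29 were enrolled by December 2025, leaving 62 − 29 = 33 of the planned sample still to enrol at that date. The report should say how many children contribute checklist data at each visit.

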### Outcomes Measures

#### Primary Outcome

##### Uncorrected Visual Acuity

We use an international standard visual acuity chart to assess visual acuity, record uncorrected visual acuity (UCVA) results in decimal notation, and subsequently convert them into logMAR format for statistical purposes. The complete disappearance of symptoms such as visual fatigue and exotropia, the restoration of distant vision, and the achievement of a visual acuity of 5.0 on the visual acuity chart are indicative of a cure; the basic disappearance of symptoms with an improvement of 3 to 5 lines on the visual acuity chart is indicative of marked efficacy; a significant alleviation of symptoms with an improvement of 2 lines on the visual acuity chart is indicative of efficacy; no change in symptoms with an improvement of 1 line on the visual acuity chart is indicative of inefficacy. The brightness of the visual acuity chart box must meet the latest national standards, which stipulate that the brightness of the visual acuity chart box should not be less than 200 cd/m^2^. We check the brightness of the examination room, as it affects the size of the pupil and use moderate appropriate lighting, with a diameter of the pupil around 3 mm being optimal.

##### Axial Length

We measure AL using ophthalmic A-ultrasound, obtain 5 readings with differences between them all less than 0.05 mm, and take the average. Normal AL for adolescents ranges from 22 to 24 mm, and values outside this range represent refractive errors.

### Secondary Measures

#### Spherical Equivalent

One drop of 1% cyclopentolate is instilled at 0, 5, and 20 minutes to induce cycloplegia in both eyes. Fifteen minutes after instillation, cycloplegia affects the pupillary light reflex and the size of the pupil. Automatic cycloplegic refraction is performed using an automatic refractor (KR-8800, Topcon). Three readings are obtained for each eye, and the average is calculated until the desired precision (spherical and cylindrical refractive power of 0.25 D and axis of 5°) is achieved. We calculate the spherical equivalent (SE) refraction as the sum of the spherical value and half the cylindrical value.

#### Amplitude of Accommodation

We determine the ability of the lens to change refractive power in response to near stimuli using the negative lens method. Refractive status is corrected using a comprehensive refractor (RK-F2, Canon, Japan), with the near visual target fixed at 40 cm. We instruct the participants to fixate on the line above the best vision on the near visual acuity chart and gradually add negative lenses in increments of −0.25 D until the participant experiences persistent blur, at which point we restore the previous degree. The amplitude of accommodation (AMP) is calculated as the total degree of added negative lenses (taking the positive value) plus 2.50 D (Figure 5).

**Figure 5. F5:**
[figure not shown]
Study schedule of measurements at different time points. AL: axial length; AMP: amplitude of accommodation; SE: spherical equivalent; UCVA: uncorrected visual acuity.

### Data Analysis

All data will be analyzed using SPSS version 28.0 and GraphPad Prism version 10.3.1 statistical software. For normally distributed data, results will be described as mean (SD) and analyzed using the *t* test. For nonnormally distributed data, results will be described as median (IQR) and analyzed using the Wilcoxon rank sum test for within-group comparisons and the Mann-Whitney *U* test for between-group comparisons. A 2-sided *P* value of .05 will be considered statistically significant. Missing data will be handled using expectation maximization, last observation carried forward, or listwise deletion.

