### Sample Size

Using G*Power software to calculate the sample size, based on the preliminary pilot study results, the expected efficacy rate in the manipulation treatment group is above 80% (*P*<.05). Therefore, we set an expected effect size of 0.8. To detect between-group differences with 80% statistical power (*β*=.20), we choose a 2-tailed α level of .05. With an allocation ratio of 1:1, the required sample size was 52 participants (26 per group). Considering a 20% expected dropout rate, the final sample size was set at 62 participants (31 per group).

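### The observed distribution decides both the test and the reported quantity, so no single between-group analysis is fixed for UCVA or axial length

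*Protocol article*

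**What the plan says.** All references are to the protocol article.

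- **Data Analysis** gives two branches. The first: "For normally distributed data, results will be described as mean (SD) and analyzed using the" t test. The second: "For nonnormally distributed data, results will be described as median (IQR) and analyzed using the Wilcoxon rank sum test for within-group comparisons", with the Mann-Whitney U test between groups. Significance is a two-sided P value of .05. No criterion for normality is given, nor whether it is judged per arm, per visit, or on raw or change scores.
- **Primary Outcome** names two variables. UCVA is taken from a chart, with "results in decimal notation, and subsequently convert them into logMAR format for statistical purposes". The same paragraph grades response by lines gained, for example "an improvement of 2 lines on the visual acuity chart is indicative of efficacy". AL is the average of five ultrasound readings in mm.
- **Study Design** calls the trial a noninferiority trial, with assessments at baseline and weeks 4, 8 and 10. **Expected Findings** anticipates results for AL, UCVA, spherical equivalent (SE) and amplitude of accommodation (AMP) that are no worse than with the drug.
- **Sample Size** says "we set an expected effect size of 0.8" and, with a two-tailed α of .05, "To detect between-group differences with 80% statistical power". From this, "the required sample size was 52 participants (26 per group"). It names neither the test nor the outcome.

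**The concern.** The rule lets the data settle two things that should be settled beforehand: which test decides a primary outcome, and what quantity is reported for it. The t-test branch targets a difference in means. The rank branch, as printed, yields a median with IQR for each arm and a P value, and no between-group difference.

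This matters in three ways here. UCVA is coarse and AL is continuous, so the two primary outcomes may end in different branches. Each outcome has three post-baseline visits, so one outcome may be reported as a mean difference at one visit and as two medians at the next. And a noninferiority claim rests on the size of a difference on the outcome's own scale, which a Mann-Whitney P value does not give.

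**Working it through.** **1. The plan's own figure.** Inputs from Sample Size: effect size 0.8 (taken as a standardized mean difference, which the article does not say), two-sided α .05, power 80%, 1:1 allocation. The two-sample t test with the noncentral t distribution needs 25.52 per group, rounded up to 26, so 52 in total; power at 26 per group is 0.807. The stated 52 is therefore what a t test gives.

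**2. The same effect with the rank test.** Mann-Whitney n = t-test n ÷ asymptotic relative efficiency (ARE).

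- Normal parent, ARE = 3/π = 0.955: 25.52 / 0.955 = 26.7, so 27 per group (54 in total). Power at 26 per group is 0.789, against 0.807: 1.8 points lower.
- Lower bound, ARE = 0.864: 25.52 / 0.864 = 29.5, so 30 per group (60 in total). Power at 26 per group is 0.746: about 6 points lower.

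**3. How often the rule switches.** The article gives no normality check and no SD, so these are assumptions: Shapiro-Wilk at .05, rank branch if either arm fails, each visit checked separately, 26 per arm, three visits with correlation 0.8, normal latent scores rounded to whole lines, 2000 runs per setting. Each range covers no effect and an effect of 0.8; the switching columns also cover the three visits where relevant.

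| Assumed SD of UCVA (lines) | Rank branch at a given visit | Test differs between visits | Type I error of the two-stage rule |
|---|---|---|---|
| 1 | 98.9–99.4% | 2.2–2.6% | 5.9% |
| 1.5 | 59.6–62.9% | 62.9–64.0% | 5.6% |
| 2 | 31.6–35.0% | 60.6–63.2% | 5.4% |
| 3 | 16.8–19.4% | 39.6–40.8% | 4.8% |

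The simulation error on a 5% rate is √(0.05 × 0.95 / 2000) = 0.5 points.

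**4. Truly normal, continuous data.** Two arms tested at .05 give 1 − 0.95² = 9.75% rank branch per visit. If visits were independent, the test would differ between visits in 1 − 0.9025³ − 0.0975³ = 1 − 0.735 − 0.001 = 26.4% of trials. The simulation with correlation 0.8 gave 25.2%; runs with 25 to 31 per arm gave about 20% to 27%. Under this check, AL would switch too, even if perfectly well behaved.

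**5. Power on whole-line scores at effect 0.8.** For SDs of 1, 1.5, 2 and 3 lines:

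- t test: 0.774, 0.792, 0.801, 0.791
- Mann-Whitney: 0.748, 0.773, 0.779, 0.769
- two-stage rule: 0.748, 0.777, 0.797, 0.789

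With no effect, the t test rejected in 4.6% to 5.8% of runs. In these settings the coarse scale alone is no reason to leave the comparison of means. Skewed data were not simulated.

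**The case against.** Much of the case on the other side stands, and it limits the point.

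- **UCVA need not fail a normality check.** A reader might infer that the rule will send UCVA to the rank test. The article does not support that. The outcome turns on an SD it does not give and a check it does not name, and equal whole-line steps in the analysed logMAR value are themselves an assumption: lines appear only in the response grading.
- **Checking per visit is an inference.** It is the natural reading of Data Analysis, but not its wording. A condensed article may also leave the normality criterion to a fuller document, so its absence is not the defect.
- **The sample size is not shown to be wrong on this ground.** A reader might infer a trial sized for the wrong test. But Sample Size names no test; the t test is inferred because it reproduces 52. The difference is one participant per group with a normal parent, and 31 per group are planned before dropout.
- **The false-positive rate is not inflated.** The two-stage rule stays near 5%.
- **Always using the t test would not by itself establish noninferiority.** The t-test branch names no confidence interval either, and no margin is stated. A Mann-Whitney analysis can also carry a Hodges-Lehmann interval, though the article names none.

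None of this removes the core. The data-dependent choice is a printed rule, not an omitted detail, and an analysis plan that fixed one test would contradict it.

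**Conclusion.** The point holds in limited form. Data Analysis selects test and summary from the observed distribution and fixes no single between-group analysis for UCVA or AL. The reported quantity may therefore differ between the two primary outcomes and between weeks 4, 8 and 10.

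How often this happens cannot be pinned down from the article; the ranges in the table rest on the assumed Shapiro-Wilk rule, the whole-line rounding and SDs of 1 to 3 lines. The loss of power is minor: about 2 points with a normal parent, about 6 at the theoretical worst.

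The damage is to interpretation: the estimand is left to the data, and the rank branch offers no difference in logMAR or mm for a noninferiority conclusion. This should be corrected, but it does not invalidate the design. The missing noninferiority margin and the derivation of the 0.8 effect size are separate issues.

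**What to change.** In Data Analysis, delete the normality-dependent choice and replace it with wording such as:

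*UCVA (logMAR) and AL, and likewise SE and AMP, will be compared between groups by the difference in means with a two-sided 95% confidence interval, from one prespecified linear model adjusted for the baseline value, whatever the observed distribution. The Mann-Whitney U test with the Hodges-Lehmann difference and its interval will be reported as sensitivity analyses only.*

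Sample Size should also say which test and outcome the 52 refers to. With a comparison of means, 52 evaluable participants stays as computed for an effect size of 0.8. If the rank test were made primary instead, the figure would be 54 with a normal parent and 60 at the lower bound of efficiency.

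The cost is wording: no extra participants, visits or measurements, since baseline values are already collected. It does need a dated and justified amendment before the final analysis, because the article's Results section reports 29 children enrolled and already comments on UCVA and AL.
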